**Figure 1 figure1:**
[figure not shown]
Flowchart of the study process
FSS, Fatigue Severity Scale; FAS, Fatigue Assessment Scale; K-mBI, Korean modified Barthel Index; K-MoCA, Korean Montreal Cognitive Assessment; K-NIHSS, Korean National Institutes of Health Stroke Scale; K-PHQ-9, Korean Patient Health Questionnaire; mRS, modified Rankin Scale.

### Eligibility

Eligibility criteria and other details are listed in Textbox 1.

Inclusion criteria, exclusion criteria, and dropout criteria.
**Inclusion criteria**
Men and women aged 19 to 80 years.Diagnosed with ischemic stroke induced by small-vessel disease in the Trial of Org 10172 in Acute Stroke Treatment (TOAST) classification within 90 days of screening based on new neurologic and brain imaging (computed tomography or magnetic resonance) findings to support them.Participants had no communication problems and voluntarily agreed to participate.
**Exclusion criteria**
Diagnosis of degenerative brain diseases (eg, Parkinson’s disease, Alzheimer disease, etc).Have a brain condition other than ischemic stroke (eg, brain tumor, traumatic brain injury, arteriovenous malformation, Moyamoya disease, and stroke due to these conditions).Unstable vital signs at screening (eg, systolic blood pressure greater than 160 mm Hg despite taking blood pressure medications).Serious medical condition (eg, liver cirrhosis, chronic kidney disease stage V, or severe heart failure of New York Heart Association (NYHA) grade III or greater).History of malignancy, including leukemia and lymphoma, within the past 5 years.Hepatic and renal dysfunctions.Aspartate aminotransferase, alanine aminotransferase ≥2 times the upper limit of normal at screening.An estimated glomerular filtration rate < 60 mL/min/1.73 m2 at screening.Within 24 hours of onset.Patients with Korean National Institutes of Health Stroke Scale (K-NIHSS) score 21 to 42.Pregnant, nurses, or women of childbearing potential who have negative pregnancy test results and have not agreed to use contraception during the study.Previously experienced hypersensitivity after taking HH333’s constituent medicines *Scutellariae radix*, *Coptidis rhizoma*, *Phellodendri cortex*, *Gardeniae fructus*, and *Rhei rhizoma*.Any other study medications administered within 30 days prior to screening.Patients who have not been administered the study medication or who have participated in a simple observational clinical trial are eligible.Difficulty taking the doses required in this study.Judged by the investigator as nonconformity for participation in the trial for any reason.Plans to use anticoagulants during the study or have difficulty discontinuing them.
**Dropout criteria**
If the researcher determines that it is not appropriate for the study to continue according to the dropout criteria, the researcher may stop the treatment and evaluation and drop the participant. Participants may also drop out of the study at any time of their free will. The dropout criteria were as follows:Found not to meet inclusion or exclusion criteria after screening.Patients or caregivers withdraw consent during the study period.Patients or caregivers request to discontinue the study or refuse treatment during the study.Participants cannot be traced.According to the judgment of the investigator, the patient is no longer able to participate in the study because of adverse events or comorbidities.Study medication compliance <80%.Participation in another clinical trial.Judged by the investigator as unfit to continue the study for any other reason.

### Recruitment

A total of 236 patients with ischemic stroke induced by small-vessel disease will be recruited through walk-in or hospital and school bulletin boards, public transportation billboards, newsletters, and other online advertisements. Participants who wish to participate will receive the consent form and provide written consent of their own free will. Multimedia Appendix 1 presents the research consent form. Participating in the study will be decided if the researcher determines that they are suitable through the screening process. The screening items were as follows: demographic information, medical history, history of ischemic stroke, medications, physical examination, vital signs, physical measurements, laboratory findings, electrocardiogram, and evaluation of the inclusion and exclusion criteria. All data were simultaneously recorded in a case report form.

### Randomization, Blinding, and Allocation Concealment

A total of 236 participants who met the criteria were assigned to the HH333 or control group at a ratio of 1:1 by a statistician independent of this clinical study, using the block randomization method with R 4.4.0 (Comprehensive R Archive Network). Patients and investigators will be blinded to prevent access to the allocation results. Patients will be blinded to the study medication they are administered because they are taking either the treatment medication or a placebo. The treatment medication and placebo will be identical in size, shape, and appearance and packaged in the same type of packaging.

For allocation concealment, an independent statistician who generates the random numbers delivers a randomization code to each clinical trial site in a sealed, impermeable envelope. The investigators at each site will open the randomization envelopes in sequence in front of the patients to assign participants, and the open envelopes will be kept separate.

### Interventions

HH333 or placebo capsules (one dose: 2 capsules, 800 mg) will be orally administered with water once a day on an empty stomach after waking for 720 days. HH333 is an herbal medicine manufactured by Kyungjin Pharmaceutical Co, Ltd. (Icheon, Republic of Korea). It is a capsule formulation derived from 80% ethanol extracts of *Scutellariae radix, Coptidis rhizoma, Phellodendri cortex, Gardeniae fructus*, and *Rhei rhizoma* (Table 2). The placebo was a capsule manufactured by Kyungjin Pharmaceutical Co., Ltd. (Icheon, Republic of Korea) with the same appearance as HH333.

**Table 2 table2:** Composition of HH333.

Constituent herbs	Scientific names	Weight (g)	
*Scutellariae radix*	*Scutellaria baicalensis* Georgi (from Republic of Korea)	0.28	
*Coptidis rhizoma*	*Coptis japonica* Makino (from Republic of Korea)	0.28	
*Phellodendri cortex*	*Phellodendron amurense* Ruprecht (from Republic of Korea)	0.28	
*Gardenia fructus*	*Gardenia jasminodes* Ellis (from Republic of Korea)	0.28	
*Rhei rhizoma*	*Rheum palmatum* L. (from Republic of Korea)	0.07	
Total			1.2

Medication compliance will be recorded in patients taking either HH333 or placebo. The participants will be instructed to return the empty containers of study medications taken and the remaining medications at each visit to count the actual number of doses of study medications. Compliance was calculated as follows:

If compliance was less than 80% at any point during the study, the participant was excluded from the study

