Experiment medication administration		✓	✓	✓	✓	✓	✓	✓	✓	✓	✓		
Medication adherence^i^			✓	✓	✓	✓	✓	✓	✓	✓	✓		If needed
Concomitant treatment		✓	✓	✓	✓	✓	✓	✓	✓	✓	✓	✓	If needed
Primary efficacy endpoint: recurrence of ischemic stroke			✓	✓	✓	✓	✓	✓	✓	✓	✓	✓	If needed
Secondary efficacy endpoints^j^		✓		✓	✓	✓	✓	✓	✓	✓	✓		If needed
Exploratory endpoints^k^		✓		✓	✓	✓	✓	✓	✓	✓	✓		If needed
Safety assessments^l^			✓	✓	✓	✓	✓	✓	✓	✓	✓		If needed
Adverse events^m^		✓	✓	✓	✓	✓	✓	✓	✓	✓	✓	✓	

^a^Telephone investigation.

^b^UV: Unscheduled visit. Visiting on a day other than the original visit schedule due to an adverse event, etc.

^c^Screening performed within 14 days of informed consent.

^d^Age, sex, smoking, and alcohol history.

^e^Within 1 year prior to visit 0.

^f^Time of first onset and diagnosis (including year, month, and day if possible), date of computed tomography or magnetic resonance imaging, ischemic stroke territory, Trial of Org 10172 in Acute Stroke Treatment classification, history of stroke-related surgery, stroke risk factors, and stroke-related symptoms.

^g^Within 4 weeks prior to visit 0.

^h^Complete blood count (red blood cell, hemoglobin, hematocrit, platelet, white blood cell); biochemistry (fasting blood glucose, blood urea nitrogen, creatinine, natrium, potassium, chloride, aspartate aminotransferase, alanine aminotransferase, C-reactive protein, calcium, uric acid); urine human chorionic gonadotropin for women of childbearing age, excluding sterilization and menopause (more than 12 months since last menstrual period); premature menopause before the age of 40 years, follicle-stimulating hormone test for differential diagnosis.

^i^Drop out if <80%.

^j^Total scores of Fatigue Severity Scale (FSS), Fatigue Assessment Scale (FAS), Korean Patient Health Questionnaire (K-PHQ-9), and probability of each type of Pattern Identification (fire heat, dampness-phlegm, Qi deficiency, and Yin deficiency).

^k^Total scores of the Korean National Institutes of Health Stroke Scale (K-NIHSS), Korean modified Rankin Scale (K-mRS), Korean modified Barthel Index (K-mBI), Korean Montreal Cognitive Assessment (K-MoCA).

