### Sample Size

In previous studies, ischemic stroke recurrence rates of 12.5%-12.8% over 24 months with conventional antiplatelet therapy (aspirin or dipyridamole) [22] and 1.7% over the same period with HH333 [19] were reported. Therefore, the sample size was 106 patients per group and 212 patients in total at 2 years with a control group (P_2_=0.125-0.128), HH333 group (P_1_=0.017), a significance level (α) of 5% and a target power of 80%. Finally, a dropout rate of 10% was considered, resulting in a sample size of 118 patients per group for a total of 236 patients.

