### Statistical Analysis

All statistical analyses were two-sided with a 5% significance level. The statistical program SAS (version 9.4 or more, SAS Institute) was used for the analysis. If at any point there are missing values or participants are dropped before the end of the study, the data will be treated as missing data. All data obtained from the participants were analyzed in 3 forms: full analysis set, per-protocol set, and safety set. Efficacy analysis will be conducted using the results of the full analysis set as the main analysis, and a per-protocol set analysis will be conducted separately to evaluate whether there are differences from the full analysis set results. Safety analysis was performed on the safety set and the safety of the study medications was evaluated. The full analysis set includes all data from participants with at least one efficacy assessment at the primary outcome after taking the study medication. The per-protocol set included participants who were eligible for full analysis and successfully completed the study. The safety set included all data from participants who received at least one dose of the study medication.

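### The 80% compliance rule lets recurrence follow-up end on post-randomisation behaviour, so primary outcomes are lost to the main analysis

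*Protocol article*

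**What the plan says.** The rule appears three times in the protocol article.

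- Interventions, without condition: "If compliance was less than 80% at any point during the study, the participant was excluded from the study".
- Table 1, footnote i, also without condition: "Drop out if <80" percent. It is attached to the compliance row, which is ticked at visits 2 to 10, nine scheduled checks.
- Dropout criteria (Textbox 1): "Study medication compliance <80" percent is a listed criterion, but the lead-in is permissive: "the researcher may stop the treatment and evaluation and drop the participant".

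Statistical Analysis says that if "participants are dropped before the end of the study, the data will be treated as missing data". The main efficacy analysis uses the full analysis set: "The full analysis set includes all data from participants with at least one efficacy assessment at the primary outcome after taking the study medication". The comparison set is described thus: "The per-protocol set included participants who were eligible for full analysis and successfully completed the study". The Primary Endpoint section counts recurrence within 750 days but ties it to the time on study medication. Efficacy Analysis models recurrence as a binary outcome by logistic regression. Under Sample Size, "a dropout rate of 10% was considered", with no split by cause.

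**The concern.** Compliance is measured after randomisation. It can depend on tolerability, and so on treatment, and on illness or cognition, and so on stroke risk. If low compliance ends recurrence assessment, the primary outcome goes unobserved for reasons that may be related to both. An analysis plan can choose how to handle a missing outcome, but it cannot recover a stroke that nobody recorded.

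The full analysis set is meant to give the main result and the per-protocol set to check it. If compliance failures are removed during conduct, the two sets move towards each other and the check loses value. Removals under the rule also draw on the single 10% dropout allowance.

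**Working it through.** **1. The plan's own figure.** Inputs from Sample Size and Statistical Analysis: 1.7% v 12.5%, two-sided 5%, 80% power. The pooled normal formula gives n0 = [1.960·√(2·0.071·0.929) + 0.842·√(0.017·0.983 + 0.125·0.875)]² / 0.108² = 87.6, so 88 per group. The continuity correction, n = (n0/4)·[1 + √(1 + 4/(n0·0.108))]², gives 106. Then 106/0.90 = 117.8, so 118. The stated 106 and 118 are reproduced.

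**2. Planned events at 118 per group.** HH333: 118 × 0.017 = 2.0. Control: 118 × 0.125 to 0.128 = 14.8 to 15.1.

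**3. What happens to a removed participant.** The first compliance check and the first recurrence assessment are both at visit 2, so most removed participants qualify for the full analysis set. If they had a recurrence before removal, it counts. If they were event-free, their status to day 750 is unknown and the logistic model has no censoring. They are either left out or coded as event-free.

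**4. Effect under no true difference.** The risk is 12.5% in both groups. Removal fractions f and risk ratios RR (removed v rest) are assumptions, because the documents give neither.

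(a) All removed participants left out, as if removed before any event. Risk among the rest = 0.125/(1 − f + f·RR).

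| Removed, HH333 v control | RR | Risk among the rest | Odds ratio |
|---|---|---|---|
| 10% v 10% | 1.5 to 3 | equal | 1.00 |
| 20% v 10% | 1.5 | 11.4% v 11.9% | 0.95 |
| 20% v 10% | 3 | 8.9% v 10.4% | 0.84 |
| 30% v 10% | 1.5 | 10.9% v 11.9% | 0.90 |
| 30% v 10% | 3 | 7.8% v 10.4% | 0.73 |
| 10% v 30% | 3 | 10.4% v 7.8% | 1.37 |

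(b) Removal at mid-follow-up, equal risk, 30% v 10%, removed participants coded event-free. Observed risk = 0.125·(1 − f/2), which is 10.6% v 11.9%, odds ratio 0.88.

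(c) As (b), but those removed event-free are left out and recurrences before removal are kept. Events = 0.125·(1 − f/2) = 0.10625 v 0.11875. Non-events = 0.875·(1 − f) = 0.6125 v 0.7875. Odds ratio = (0.10625/0.6125)/(0.11875/0.7875) = 1.15.

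Cases (b) and (c) have the same removals and lie on opposite sides of 1.

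**5. Dropout allowance.** With an assumed constant, independent probability q of failing each of nine checks, the fraction removed is 1 − (1 − q)⁹: 16.6% at q = 2% and 24.0% at q = 3%. The 10% allowance is used up by this rule alone at q = 1 − 0.9^(1/9) = 1.16%. If 20%, 30% or 40% are lost in total, 94, 82 or 70 per group remain. Power by the formula without continuity correction is then 83–84%, 77–79% or 70–72%, against 87–88% at 106.

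**The case against.** Several points on the other side stand.

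- A reader might infer that the main analysis is restricted to adherers. The full analysis set has no compliance condition, and it counts a recurrence before removal.
- The only sentence that says evaluation stops is permissive, while Interventions and Table 1 are unconditional and do not define what stops. The passages conflict, so loss of every later recurrence is not certain. Discretion is no cure, however, because follow-up would then depend on the investigator's judgement. Adverse events are collected until 30 days after the end of administration, which could catch some early recurrences.
- A reader might infer a bias in favour of HH333. That needs unequal removal or different reasons for it. The capsules look identical, and the Discussion cites mild adverse events in 2% of patients in an earlier safety study, so strongly unequal removal is not documented. The illustrated odds ratios are also far from the design value of about 0.12, i.e. (0.017/0.983)/(0.125/0.875).
- A reader might infer that the 10% allowance fails to cover these removals. It is not split by cause, no non-compliance rate is given, and the compliance formula is not visible in the text at hand, so whether compliance is per interval or cumulative is unknown.
- A reader might infer that the per-protocol set loses many recurrences. Recurrence is not a listed dropout criterion. Successful completion is merely undefined, which leaves that possibility open.

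The link between the endpoint and time on medication could be defended as a deliberate on-treatment question. That does not justify ending observation, since an on-treatment analysis can be derived from full follow-up but not the reverse.

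**Conclusion.** The concern holds in a limited form. Followed as written, the plan loses primary outcomes because of post-randomisation compliance, and no passage restores them. The main comparison then depends partly on adherence and moves towards the per-protocol comparison it should be checked against.

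Direction and size cannot be read from the documents. Under no true effect the odds ratio stays at 1.0 if removal is equal and for similar reasons. Under the assumed unequal removals above it ranges from 0.73 to 1.37. With about 2 v 15 planned events, a few unobserved recurrences could alter the result. Pressure on the dropout allowance is secondary, at a rate the documents do not give.

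This should be corrected during conduct, because uncollected outcomes cannot be recovered later. The Results section reports 12 of 236 participants randomised by 13 November 2024, so at that date nearly all follow-up could still be protected.

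**What to change.** 1. Reconcile Interventions, Table 1 footnote i and the dropout criteria, and state that low compliance or stopping capsules does not end recurrence follow-up. Whether and when capsules are stopped is a separate matter for the sponsor.
2. Amend the Primary Endpoint section so that recurrence counts to day 750 whether or not capsules are still taken, and align the period named in Efficacy Analysis. Without this, recurrences after stopping might be collected but not counted.
3. Amend Statistical Analysis so that the main analysis includes all randomised participants, with follow-up collected regardless of compliance and ended only by withdrawal of consent to follow-up.
4. Use the 80% threshold only to define the per-protocol set: compliance up to first recurrence or end of treatment, whichever comes first, with a recurrence not counted as failure to complete.

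The cost is a wording amendment and continued visits or contacts for those who stop capsules. A telephone contact already exists at visit 11, but Outcome Measurements specifies face-to-face assessment and the endpoint needs neurological examination and imaging, so a suspected recurrence still requires the usual work-up. Including non-adherers will dilute the effect somewhat. The sample size of 106, inflated to 118 per group, is unchanged.

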### Outcome Measurements

The clinical efficacy of HH333 in patients with ischemic stroke induced by small-vessel disease will be evaluated based on whether ischemic stroke recurrence occurs after administration of HH333. Furthermore, the effects on quality of life and fatigue will be evaluated by measuring FSS, FAS, and K-PHQ-9 scores, and changes in pattern identification probability will be investigated to provide basic data for the Korean medicine treatment of stroke. The K-NIHSS, mRS, K-mBI, and K-MoCA will be used to assess functional improvements related to ischemic stroke. All outcome measurements will be conducted through face-to-face visits.

### Primary Endpoint: Recurrent Ischemic Stroke

Recurrent ischemic stroke within 750 days while taking the study medication was investigated. Recurrent ischemic stroke is defined as a new neurological finding supported by new imaging findings. New neurological findings corresponded to the sudden onset of neurological symptoms identified on neurological examinations that did not occur prior to study participation. New radiological findings are abnormal findings on brain imaging (computed tomography or magnetic resonance), which can explain new neurological findings that did not exist before study participation. The investigation will be conducted on days 30, 90, 180, 270, 360, 450, 540, 630, 720, and day 750, which is 30 days after the end of administration.

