### Efficacy Analysis

#### Analysis of Primary Efficacy Endpoints

The number of events will be presented for ischemic stroke recurrence during the 2-year study medication treatment period, the odds ratio of stroke recurrence will be calculated, and logistic regression analysis will be performed with ischemic stroke recurrence as the dependent variable and other factors such as HH333 treatment, risk factors, and neurological deficits as independent variables.

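### The primary endpoint has two incompatible counting windows (to day 750, or only the treatment period ending at day 720), is tied to being on medication, and has a telephone assessment although all outcomes are said to be face-to-face

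*Protocol article*

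**What the plan says.** All references are to the protocol article.

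- **Primary Endpoint: Recurrent Ischemic Stroke.** The definition reads "Recurrent ischemic stroke within 750 days while taking the study medication was investigated". The same paragraph lists the assessment days and describes the last as "day 750, which is 30 days after the end of administration". A recurrence needs a new neurological finding on examination, supported by new imaging.
- **Interventions.** Capsules "will be orally administered with water once a day on an empty stomach after waking for 720 days".
- **Analysis of Primary Efficacy Endpoints.** "The number of events will be presented for ischemic stroke recurrence during the 2-year study medication treatment period", followed by an odds ratio and logistic regression.
- **Abstract (Methods), Study Design and Table 1.** All three schedule recurrence assessment through day 750. Table 1 ticks the primary endpoint at Visits 2 to 11, and Visit 11 covers days 745-755.
- **Outcome Measurements.** "All outcome measurements will be conducted through face-to-face visits".
- **Table 1, footnote a.** Visit 11 is a "Telephone investigation".
- **Statistical Analysis.** The full analysis set is the main efficacy analysis. Data from participants who are dropped are treated as missing.
- **Dropout criteria, Interventions and Table 1, footnote i.** Participants with compliance below 80% leave the study, and the researcher may end both treatment and evaluation.

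**The concern.** The definition sets two conditions that cannot both hold after day 720: an event may occur up to day 750, and the participant must be taking study medication. The analysis section then counts only the treatment period. A confirmed stroke on day 735 falls inside the 750-day limit, but fails the on-medication condition and falls outside the analysis period. This is the sole primary endpoint and few events are expected. If the conflict stands, the counting rule could be chosen after the data are seen.

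The on-treatment wording raises a second question. Read literally, neither the definition nor the analysis text counts a stroke that follows early discontinuation. If stopping is related to treatment or prognosis, leaving those strokes out weakens the randomised comparison that a full-analysis-set main analysis is meant to protect.

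The third issue is the mode of assessment. The primary endpoint is ticked at a telephone contact, yet the definition requires an examination finding and imaging, and another section says every outcome is measured in person.

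**Working it through.** **1. The texts side by side, for a confirmed stroke on day 735 in a participant who completed 720 days of dosing**

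| Text | Does it count? |
|---|---|
| Primary Endpoint, 750-day limit | Yes |
| Primary Endpoint, on-medication condition | No |
| Analysis of Primary Efficacy Endpoints (treatment period) | No |
| Abstract, Study Design, Table 1 (assessed to day 750) | Assessed as primary endpoint |

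**2. The plan's own figure.** Inputs from Sample Size and Statistical Analysis: p1 = 0.017 (HH333), p2 = 0.125 (lower control value), two-sided α = 0.05, power 80%, 1:1.

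Uncorrected: n = [1.960·√(2p̄(1−p̄)) + 0.842·√(p1(1−p1) + p2(1−p2))]² / (p2−p1)², with p̄ = 0.071 and p2−p1 = 0.108. This gives 87.6, so 88 per group.

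With continuity correction: (n/4)·[1 + √(1 + 4/(n·0.108))]² = 105.3, so 106 per group. Then 106/0.9 = 117.8, so 118 per group and 236 in total.

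Both stated figures reproduce. The window conflict is not a sample-size error.

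**3. Events expected in days 721-750.** Assumptions, not in the document: constant hazard, 24 months = 730 days, 118 per arm all followed, and each arm keeping its own hazard after dosing stops.

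Hazard h = −ln(1−p)/730:
- Control: −ln(0.875)/730 = 0.00018292 per day
- HH333: −ln(0.983)/730 = 0.00002349 per day

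Events in the window = 118·[exp(−720h) − exp(−750h)]:
- Control: 118·(0.87660 − 0.87180) = 0.57
- HH333: 118·(0.98323 − 0.98254) = 0.08
- Total: 0.65

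Expected events to day 720 are 14.56 + 1.98 = 16.54, and to day 750 are 15.13 + 2.06 = 17.19. The disputed window holds 0.65/17.19, or about 4% of events. Treating the count as Poisson, the chance of at least one event there is 1 − exp(−0.65), about 48%.

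**4. Sensitivity.** With control at 12.8%, the control figure is 0.58. If the HH333 arm reverted to the control hazard off drug, it would contribute 0.63-0.65 events instead of 0.08, for about 1.2 in total across both arms.

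**5. Could one event matter?** Fisher's exact test, used only as an illustration because logistic regression is planned, at 106 per arm:

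| HH333 vs control events | p |
|---|---|
| 2 vs 13 | 0.0056 |
| 2 vs 12 | 0.010 |
| 2 vs 10 | 0.033 |
| 2 vs 9 | 0.059 |

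The planning rates imply about 106·0.017 = 1.8 and 106·0.125 = 13.25 events, close to 2 vs 13. Losing one control event there changes nothing. One event crosses 0.05 only if the effect is already smaller than planned.

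**The case against.** The strongest case against is that the point is small and mostly editorial. Fewer than one expected event is at stake at each arm's own hazard, the sample size is unaffected, and a one-event change of significance appears only for counts chosen near the threshold. All of that stands, and it limits the severity.

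A reader might infer that a telephone assessment makes the endpoint impossible to establish at Visit 11. The document does not support that. Table 1 marks the primary endpoint as available at an unscheduled visit if needed, so a call can flag a suspected recurrence that is then examined and imaged. Confirmation detail is also something an article may leave to the full protocol. What remains is the categorical face-to-face statement, which conflicts with footnote a.

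A reader might also add strokes lost after early discontinuation to the size of the window conflict. Those losses arise mainly from the dropout criteria, the compliance rule and the missing-data rule, so they do not belong in the 0.65.

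Finally, nothing in the document makes day 720 the only proper cut-off. Four places run to day 750, and Visit 10 itself spans days 705-735. Day 720 sits closer to the 24-month planning rates, and day 750 closer to the schedule. Either works if used throughout.

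**Conclusion.** The contradiction is in the current text and does not depend on anything an analysis plan might add. The definition and the analysis text give different windows, the definition cannot be satisfied after day 720, and both make the endpoint conditional on treatment while the main analysis uses the full analysis set. The face-to-face statement is wrong for Visit 11.

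The expected effect is small: about 0.65 of roughly 17 events (0.57 control, 0.08 HH333), given a constant hazard at the planning rates, 730 days for 24 months and 118 per arm. If HH333 reverted to the control hazard off drug, it would be about 1.2 events. At the planned effect size this would not change the conclusion; in a borderline result it could. A reader might infer that the trial's significance hangs on the window, and the figures do not support that. It should be fixed because the sole primary endpoint needs one meaning before the data are seen.

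**What to change.** Before unblinding:

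1. State one identical window in Study Design, Primary Endpoint and Analysis of Primary Efficacy Endpoints. Either use day 720, which is close to the 24-month planning rates, and report days 721-750 separately; or use day 750 and align the analysis section. Assign events by date of stroke onset, not by visit.
2. Delete the on-medication condition, and the treatment-period wording in the analysis section, so that strokes count from randomisation whether or not study medication is still being taken.
3. For item 2 to work, reconcile the Dropout criteria, the compliance text in Interventions, Table 1 footnote i and the missing-data sentence in Statistical Analysis, so that recurrence continues to be ascertained after study medication stops. This concerns outcome follow-up only.
4. Amend Outcome Measurements to acknowledge the telephone visit, and state that a recurrence reported there counts once examination and imaging, from an unscheduled visit or from records, confirm it.

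Cost: at each arm's own hazard, under one expected event moves in or out of the primary count. Items 1 and 4 are wording. Items 2 and 3 also need modest continued contact with participants who stop study medication. With 12 of 236 participants randomised and no analysis done at the time of reporting, the change could be made early.

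### The clinical part of the primary endpoint, read naturally, leaves out a new infarct that brings back or worsens an earlier deficit, and is at best ambiguous on the point

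*Protocol article*

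**What the plan says.** The protocol article, under Primary Endpoint: Recurrent Ischemic Stroke, sets a two-part rule: "Recurrent ischemic stroke is defined as a new neurological finding supported by new imaging findings". Both parts are required.

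- The neurological part is "the sudden onset of neurological symptoms identified on neurological examinations that did not occur prior to study participation".
- The radiological part is an abnormality on CT or MR, "which can explain new neurological findings that did not exist before study participation".

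Two eligibility rules in Textbox 1 bear on this. The index stroke must be a small-vessel stroke by TOAST "classification within 90 days of screening based on new neurologic and brain imaging" findings. The only severity exclusion is "Patients with Korean National Institutes of Health Stroke Scale (K-NIHSS) score 21 to 42", so a K-NIHSS score of up to 20 is allowed at entry.

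No other section says whether sudden worsening of an existing deficit, or return of one that had resolved, counts as a recurrence.

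**The concern.** In this population the index symptoms are always part of the history before entry, and many participants may still have them. If an earlier symptom cannot be a new neurological finding, a fresh infarct that brings back or aggravates, say, the same-side weakness fails the neurological part. A new lesion on imaging does not rescue it, because both parts are required.

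The trial plans on few primary events, so each true recurrence that the definition leaves out costs information. The wording also leaves room for two readings of the primary endpoint in a trial run at three hospitals.

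**Working it through.** **1. Reading the two sentences.**

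- *Neurological sentence.* The closing clause most naturally qualifies the symptoms, so a symptom present before entry cannot qualify. It can instead be attached to the sudden onset; a fresh onset of the same symptom would then qualify. Under neither reading is worsening of a persisting deficit named.
- *Radiological sentence.* By word order the closing clause follows the neurological findings. Taken that way it only repeats the word new, and nothing would then require the lesion itself to be new. It more sensibly belongs to the imaging lesion. I do not count it as a second restriction.

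**2. Reproducing the plan's sample size.** Inputs from Sample Size: control 0.125 (lower end of 0.125 to 0.128), HH333 0.017, "a significance level (α) of 5% and a target power of 80" percent, 10% dropout. From Statistical Analysis: "All statistical analyses were two-sided with a 5% significance level".

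With d = 0.125 − 0.017 = 0.108 and mean rate p̄ = (0.125 + 0.017)/2 = 0.071:

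- n₀ = [1.960·√(2·0.071·0.929) + 0.842·√(0.017·0.983 + 0.125·0.875)]² / 0.108² = 87.6
- with continuity correction, n = (n₀/4)·[1 + √(1 + 4/(n₀·d))]² = 105.3, rounded up to 106 per group
- dropout: 106/0.9 = 117.8, rounded up to 118 per group, 236 in total

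The stated 106 and 118 reproduce. At a control rate of 0.128 the same formula gives 102.

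**3. Expected events.** 106 × (0.125 + 0.017) = 15.1.

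**4. Effect of missed events.** Let m be the share of true recurrences that repeat or worsen an earlier deficit and go uncounted, equal in both arms. The documents give no value, so m is assumed. Both rates are multiplied by (1 − m), with 106 analysed per group. The continuity-corrected power solves the formula in step 2 backwards:

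- n* = n·[1 − 1/(n·d)]²
- power = Φ{[d·√n* − 1.960·√(2p̄(1 − p̄))] / √(p₁(1 − p₁) + p₂(1 − p₂))}

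At m = 0, n* = 88.3 and power is 80.3%. The uncorrected version uses n in place of n*. Fisher power is the exact binomial sum over all tables with p ≤ 0.05.

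| m | Control / HH333 rate | Expected events | Power, corrected | Power, uncorrected | Power, Fisher exact | n per group for 80%, corrected |
|---|---|---|---|---|---|---|
| 0 | 0.125 / 0.0170 | 15.1 | 80% | 87% | 86% | 106 |
| 10% | 0.1125 / 0.0153 | 13.5 | 75% | 83% | 81% | 118 |
| 20% | 0.100 / 0.0136 | 12.0 | 68% | 78% | 74% | 134 |
| 30% | 0.0875 / 0.0119 | 10.5 | 60% | 72% | 65% | 154 |

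With a control rate of 0.128 the corrected powers are 82%, 76%, 70% and 62%. The risk ratio is unchanged in every row (0.017/0.125 = 0.136), because the same factor multiplies both arms.

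**The case against.** **The wording may be innocent.** The governing sentence asks only for a new neurological finding with new imaging, and an abrupt deterioration with a fresh infarct can be read as meeting it. The article is also condensed; a full protocol or case report form not shown may settle the matter. This stands as far as it goes: the text does not plainly exclude such events. But the article itself states the definition, and its natural reading is the narrow one. If a fuller document is broader, the published wording disagrees with it.

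**A reader might infer that the restriction is stated twice and so is deliberate.** The documents do not support that, for the reason given for the radiological sentence in step 1.

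**A reader might infer that the three hospitals will count different events.** The ambiguity makes that possible; nothing in the article shows that it happens.

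**A reader might take 60% as the trial's power.** That figure is the worst cell of an assumed range under the most conservative formula. The planned analysis is logistic regression. An exact calculation for its unadjusted likelihood-ratio test gives 93%, 90%, 86% and 82% for m = 0, 10%, 20% and 30%, though that test can be liberal with so few events. At a 10% miss, only the continuity-corrected figure is below 80%.

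**The planning rates may already be narrow.** A loss against 12.5% and 1.7% arises only if the source studies used a broader definition. The article does not give their definitions, so this cannot be settled here.

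**Requiring a new deficit protects specificity.** CT or MR is accepted at entry and for the endpoint, and Table 1 schedules no study scan. An index lesion not visible on a baseline CT could look new on a later MR, and fluctuation of the old deficit would then be counted as recurrence. This stands, and the fix has to deal with it.

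**Conclusion.** The point holds in this form. Read naturally, the clinical part of the primary endpoint does not count a new infarct that causes return or sudden worsening of an earlier deficit; on the looser reading it is ambiguous, and worsening is named on neither. It matters here because all participants enter with a recent index stroke and only about 15 events are expected.

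The size of the loss is unknown. On an assumed 10% to 30% missed equally in both arms, 1.5 to 4.5 of those events are lost, and power drops by about 5 to 20 points (continuity-corrected), 4 to 15 (uncorrected) or 5 to 21 (Fisher). The harm under that assumption is lost events and power; it is not evidence of a biased treatment comparison. The definition should be corrected, with medium confidence in how much it matters.

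**What to change.** Reword the clinical part as a sudden new focal deficit, or sudden worsening or return of an earlier deficit, after randomization, explained by a new infarct on CT or MR. Attach the requirement of absence before study participation to the imaging lesion, not to the type of symptom.

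Add one guard. Where the event is worsening or return of an old deficit, imaging must show that the infarct is recent (for example acute on MR) or that it was absent on a prior scan of comparable modality.

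The cost is a sentence or two in the endpoint definition and matching items on the case report form. The remaining downside is that an index lesion missed on baseline CT could still be mistaken for a new one if the guard is applied loosely. The article reports 12 participants randomized by November 13, 2024 and no data analysis, so at that point the change could be made without knowledge of results. Any suspected event already recorded should be reclassified blind to allocation under the revised wording.
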